### Secondary outcomes

The secondary outcomes are a) the identification of possible risk factors of LTBI in a large cohort of HCWs and students, and b) the validation of the prediction models through the enrolment of a subsequent new cohort of HCWs and students at the teaching hospitals.

The following list of possible risk factors will be recorded:

Age and sex.Bacillus Calmette–Guérin (BCG) vaccination history.Previous work or stay in other countries with high TB rates including Armenia, Azerbaijan, Belarus, Bulgaria, Estonia, Georgia, Kazakhstan, Kyrgyzstan, Latvia, Lithuania, Moldova, Romania, Russia, Tajikistan, Turkey, Turkmenistan, Ukraine, and Uzbekistan.Known recent (within 6 months) exposure to TB-infected patient, which makes HCW or student a close contact of individuals with tuberculosis [31].Current smoking.Co-morbidities/ medical history (HIV, diabetes, silicosis, chronic kidney disease, solid organ transplant, malignant hematologic malignancies or undergoing chemotherapy, gastrectomy or fasting bypass, biological drugs).Median QuantiFERON-TB Gold In-Tube level (TB Ag-Nil).Occupation (doctor, nurse, laboratory technicians, paramedical personnel, “preclinical” students with no contact with patients inside the hospital, and “clinical” students attending various medical, laboratory, and surgical departments of the hospital, including the infectious disease wards).Working/ training UnitYears working as HCW

### Data management plans

All enrolled participants, who will agree to participate in the study and answer the questionnaire, will respond to a cross-sectional questionnaire survey through dedicated tool only once.

The survey contains a brief explanation of the study aims and an invitation to respond to a 9-item multiple-choice questionnaire.

During the first phase of the project, the Research Team adopted Microsoft Forms included in Microsoft Office 365 subscription of FPG and UCSC. Once the results start to roll in, the survey author is then able to use the simple built – in analytic tools within Forms to analyze the results and construct them into reports such as Excel tables. Although there are other surveying tools available (Google Forms, Survey Monkey etc.) Microsoft Forms is the standard for FPG and UCSC as all data is held securely within the university’s Office 365 tenancy. The questionnaire is created following instructions available in the Microsoft Forms web site, and responses are automatically re-directed to the Research Team.

A specific 9 items self-test questionnaire, developed for the specific purpose and never administered before, is administered to the enrolled HCWs and students (Fig 2).

**Fig 2 pone.0319568.g002:**
[figure not shown]
Health care workers and students questionnaire (English version). The specific 9 items self-test questionnaire, developed for the specific purpose and never administered before, administered to the enrolled HCWs and students.

The questionnaire was firstly validated through the following procedure

A Delphi Method structured on a panel of experts to achieve mutual agreement.The questionnaire was the object of a first validation phase on the first 25 responding subjects and results were analyzed to test its applicability and generalizability.

In addition to demographic information, a list of possible risk factors includes age and sex, Bacillus Calmette–Guérin (BCG) vaccination history, previous work or stay in other countries with high TB rates, known recent (within 6 months) exposure to TB-infected patient, current smoking, co morbidities/ medical history, median QuantiFERON-TB Gold In-Tube level (TB Ag-Nil) if available, occupation, working/ training Unit and years working as HCWs [32]. All positive QFT results on the first determination are repeated to confirm the finding. All conversions of QFTs are collected for the final analysis. No incentives will be offered to complete the survey. A first predictive model for LTBI will be set up through analysis performed by Real World Data GENERATOR.

All HCWs and students enrolled in UNIPA and in University Hospital of Bari will undergo the same methodologies adopted in FPG/UCSC.

## Statistical analysis

Descriptive statistics will be performed to characterize responses to the survey. The distribution of the qualitative variables will be shown in percentages, whereas the quantitative variable means, and standard deviations will be used after performing the Shapiro-Wilk test to verify their parametric distribution. Categorical variables will be compared using the Chi-squared test.

Logistic regression analysis will be performed to assess the association between LTBI and possible risk factors including age and sex, Bacillus Calmette–Guérin (BCG) vaccination history, previous work or stay in other countries with high TB rates, known recent (within 6 months) exposure to TB-infected patient, current smoking, co morbidities/ medical history, median QuantiFERON-TB Gold In-Tube level (TB Ag-Nil) if available, occupation, working/ training Unit and years working as HCWs.

The results of the risk-assessment analysis will be stratified according to sex, nationality, TB incidence of the country of birth and BCG vaccination and possible change in the roles of the participants and consequently in the risks of exposure.

Specific data visualization techniques will be used to provide a qualitative representation of the outcomes.

For the purposes of the project, cloud-based applications will be used to collect and store the data coming from the three healthcare centres. Data analytics will be adopted to measure the associations of risk factors with LTBI development. Finally, machine learning techniques will be used to predict the presence of LTBI with respect to health data and identified risk factors.

The final deliverable of the project will be a computerized decision support system able to deliver alerts in the case of LTBI presence.

*p-values* ≤ 0.05 will be considered statistically significant.

All the statistical analyses will be carried out using R statistical software (R Core Team, 2021).

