### The sample size

From the literature, Coppeta et al. [29] found a rate of LTBI prevalence of 2.1% in a population of Italian HCWs in Rome, and Verso et al. reported a prevalence rate of LTBI of 0.62% among Italian healthcare students and postgraduates in Palermo [26]. Therefore, we assumed a prevalence of LTBI of 1% in our population. The sample size was calculated considering the objectives of estimating the prevalence of LTBI and identifying its risk factors.

As regards the estimate based on the first outcome, considering 1) the assumed prevalence of LTBI of P = 1% in each teaching hospital involved in the research project, 2) an error estimate of d = 0.3%, and 3) a chosen confidence level of 90%, we obtained a total sample size of 2,977 subjects to be enrolled. The following formula [30] was used:

$$n=\frac{Z^{2}P\left(1-P\right)}{d^{2}}$$

where Z = Z statistic for a level of confidence (1.64 for 90% confidence level) [30]

The potential involvement of all employees and students attending medical, specialization and health professions degree courses, in the three university hospital centers involved in the project, will reasonably allow us to reach a higher sample size than the minimum target of 2,977 subjects. Indeed, for detecting an odds ratio (OR) as low as 1.69 (OR for male gender in [29]) with a type I error α=0.05 and power β=0.95, it would be required to reach a sample size of 3,503 subjects (z-test on logistic regression)

The calculation was performed using R statistical software (R Core Team, 2021).

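### About 30–35 expected LTBI cases at the stated sample sizes cannot support a joint, unpenalised logistic regression on the listed risk factors (roughly 14–22 coefficients)

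*Protocol article*

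**What the plan says.** Under The sample size, the article cites "a rate of LTBI prevalence of 2.1% in a population of Italian HCWs in Rome" and a "prevalence rate of LTBI of 0.62% among Italian healthcare students" and postgraduates in Palermo. From these, "we assumed a prevalence of LTBI of 1% in our population". It derives 2,977 subjects as a minimum for estimating prevalence and 3,503 for detecting an odds ratio of 1.69 by a z-test in logistic regression. It expects to exceed 2,977 but gives no upper figure. It states no expected number of cases.

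Under Statistical analysis: "Logistic regression analysis will be performed to assess the association between LTBI and possible risk factors including age and sex". The list goes on to BCG history, work or stay in high-TB countries, recent exposure, smoking, comorbidities, QuantiFERON level if available, occupation, working or training unit, and years as a healthcare worker. Results are to be stratified by sex, nationality, TB incidence in the country of birth and BCG, among others. For categorical data, "Categorical variables will be compared using the Chi-squared test". Machine learning is then to predict LTBI from health data and the identified risk factors.

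Secondary outcomes itemises the recorded factors. The comorbidity entry begins "Co-morbidities/ medical history (HIV, diabetes, silicosis, chronic kidney disease, solid organ transplant" and has eight items. Occupation has six groups. Validation of the prediction models in a new cohort is a secondary outcome.

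**The concern.** The information in a logistic regression on a rare outcome is limited by the number of cases, not the number of participants. The second sample-size calculation rests on one odds ratio for one covariate (sex), whereas the analysis section applies logistic regression to a list of more than ten factors, several with multiple levels. The article never sets case numbers against model size.

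Three results are at stake. The first is the risk-factor odds ratios, which are a secondary outcome. The second is the univariable comparisons, if chi-squared is used for them. The third is the prediction model, which is meant to feed a decision support system that issues alerts.

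**Working it through.** **1. The plan's sample sizes.** With n = Z²P(1−P)/d², P = 0.01 and d = 0.003, Z = 1.645 gives 2,976.6, hence 2,977. The printed Z = 1.64 gives 2,959. The 3,503 is matched to within one subject (3,502) by a logistic z-test with baseline risk 1%, odds ratio 1.69, one-sided α 0.05, power 0.95 and a standard normal covariate. Whether those settings suit sex is a separate question; both sizes are taken as printed.

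**2. Expected cases = N × prevalence.**

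| Prevalence | N = 2,977 | N = 3,503 |
|---|---|---|
| 0.62% | 18.5 | 21.7 |
| 1% | 29.8 | 35.0 |
| 2.1% | 62.5 | 73.6 |

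**3. Coefficients from the list.** Age, sex, BCG, stay abroad, exposure and smoking: 6. QuantiFERON level: 1. Occupation with six groups: 5. Years: 1. Subtotal 13.
- Comorbidities as one term: 14, or 15 with a two-level unit variable.
- Comorbidities as eight terms: 21, or 22 with a two-level unit variable.

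A unit variable with more levels would add to these counts.

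**4. Cases per coefficient.**
- At 1%: from 29.8/22 = 1.35 to 35.0/14 = 2.50.
- At 2.1%: from 62.5/22 = 2.84 to 73.6/14 = 5.25.
- At 0.62%: from 18.5/22 = 0.84 to 21.7/14 = 1.55.

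For scale, ten cases per coefficient at 1% would need 15/0.001 = 15,000 subjects for 15 coefficients and 21,000 for 21.

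**5. Zero exposed cases.** With 35 cases and no association, the chance that none is exposed is about (1 − s)³⁵ for a factor held by share s. For s = 0.5% this is 0.84; for s = 1% it is 0.70. The article gives no shares, so these are assumptions. With no exposed case, the maximum likelihood odds ratio has no finite logarithm.

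**6. Illustrative simulation.** Category shares and effects were assumed, QuantiFERON level and unit were left out, the fit was nearly unpenalised, and there were 200 runs per row.

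| N | Coefficients | Runs with a zero-case category | Median calibration slope, new data | AUC apparent / new data |
|---|---|---|---|---|
| 2,977 | 20 (eight comorbidities) | 100% | 0.16 | 0.74 / 0.59 |
| 2,977 | 13 (one comorbidity term) | 43% | 0.30 | 0.74 / 0.60 |
| 3,503 | 20 | 100% | 0.20 | 0.74 / 0.60 |
| 3,503 | 13 | 33% | 0.41 | 0.73 / 0.60 |

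A well-calibrated model has slope 1.

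**7. Chi-squared.** The expected number of exposed cases is below 5 when the factor's share is below 5/29.8 = 16.8% (N = 2,977) or 5/35.0 = 14.3% (N = 3,503). The exact hypergeometric type I error at nominal 5%, with N = 3,503 and 35 cases, is:

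| Exposed | Uncorrected | Continuity-corrected |
|---|---|---|
| 17 | 15.7% | 1.2% |
| 18 | 1.3% | 1.3% |
| 30 | 3.5% | 3.5% |
| 100 | 7.7% | 1.7% |
| 200 | 4.6% | 1.3% |

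Over every exposed count from 2 to 500, the uncorrected error peaks at 17 exposed and is lowest at 18. One more exposed participant moves it from one extreme to the other, because a single exposed case stops being significant. The corrected test never exceeds 5% but is often far below it.

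**The case against.** Several stronger readings are tempting, and the article does not support them.

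- A reader might take 21 coefficients as the minimum. The analysis section names comorbidities as a single item; the eight entries are only what will be recorded. One composite term is compatible with the text and gives 14–15.
- A reader might infer that ordinary maximum likelihood with all terms in one model is the stated method. The text says only logistic regression. Penalisation, variable selection and exact-test fallbacks may sit in an analysis plan not shown, and their absence from an article is no fault. The harm is therefore conditional on a joint, unpenalised fit.
- A reader might carry the coefficient count over to machine learning. No algorithm or model size is named, and prediction is to use identified risk factors, not necessarily the whole list.
- A reader might quote 15.7% as the error of the chi-squared test. That is its peak; many exposed counts give an error close to or below 5%. The article does not say whether a continuity correction is used, and its chi-squared sentence stands with the descriptive analyses, without naming LTBI as the comparison.
- A reader might call most cells tiny. Category shares are not given. Sparse cells are likely for comorbidities, unit levels and small occupation groups, but not for sex, and not necessarily for BCG or smoking.

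Two further points on the other side are fair. The 2,977 is a minimum, and recruitment of all staff and students at three centres could exceed it. Validation in a new cohort is planned, so inflated apparent accuracy would not go unnoticed. But validation detects a poor model without improving it, and ten cases per coefficient would take about 15,000 subjects or more at 1%. The mismatch between case numbers and the list remains on every reading.

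**Conclusion.** The concern holds in conditional form. At the stated sizes and 1% prevalence, about 30–35 cases (18–74 over the cited 0.62%–2.1%) face roughly 14–22 coefficients: about 1.4–2.5 cases each, and at most about 5 at 2.1%. No cited prevalence and no reading of the list makes a joint, unpenalised model reliable at these sizes. Stratifying the results would thin the cases further.

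The case counts and ratios rest only on the article's figures and on counting the list. The frequency of zero cells, the calibration slopes and the AUC gap rest on assumed shares and effects; they show the likely direction and rough size, not a forecast. It does not follow that estimates will certainly be undefined. That is likely for rare factors such as HIV, silicosis or transplant if they are entered separately without penalisation.

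This should be corrected in the analysis text. It does not undermine the prevalence estimate.

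**What to change.** In Statistical analysis:

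- Specify Firth (penalised-likelihood) logistic regression with profile-likelihood intervals.
- Pre-specify a short main model with comorbidities as one indicator. For example: age, sex, BCG, stay in a high-incidence country, known exposure, healthcare worker versus student, any comorbidity, and centre (three centres, two coefficients). That is 9 coefficients, or 29.8/9 = 3.3 to 35.0/9 = 3.9 cases each at 1%, which is still few enough to need the penalty. Report the remaining factors descriptively.
- Use Fisher exact or mid-p tests where any expected count is below 5.
- For prediction, use penalised regression (ridge or LASSO), or another method with its complexity controlled, and report bootstrap optimism-corrected performance before the planned validation.

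The cost is analysis-plan wording and standard packages in R, which is already the chosen software. No new data are needed, and with primary completion estimated for June 30, 2026, the wording can be settled before the multicentre analysis. The downside is that fewer factors are reported separately.

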The ongoing CROSSWORD study, aimed at collecting big data on the prevalence of LTBI in HCWs and students and the identification of possible risk factors for LTBI, in a single center, presents, as main current criticality, the monocentric nature of the study. The translation of the same methodologies of the CROSSWORD study within the research project entitled “*Implementing an interoperable web-based platform to support health surveillance against latent tuberculosis infection in health care workers and students to define prevention strategies and interventions: the evolution of CROSSWORD Study*” and the involvement of more centers will allow the creation of a shared interoperable digital platform and the definition of primary prevention strategies for LTBI.

Our research project is inspired by TB risk prediction model elaborated in a recent meta-analysis (PERISKOPE-TB) that combines a quantitative measure of T cell sensitization and clinical covariates [4]. We adopted some candidate predictors included in the final version of prognostic model described by Gupta et al.: exposure, HIV status and history of hematological or solid organ transplant [4].

Here we present the protocol of the Evolution of CROSSWORD study.

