## Procedures

### Primary outcome

The general objective of the research project is to develop an interoperable web-based platform to provide epidemiological and health surveillance against LTBI in the hospital setting. The primary outcome of the study is the prevalence of LTBI defined as 1) positive TST at enrollment, 2) tuberculin conversion defined as negative TST before enrollment and positive at enrollment, 3) subsequent positive QuantiFERON-TB Gold (QFT) test result performed on the same day as the positive TST result or within 5 days of tubulin conversion [higher response than the cut-off value of 0.35 IU/ ml of INF-γ was detected in at least one test tube (TB1 or TB2)], 4) chest imaging excluding pleural and/or pulmonary lesions suggestive of active tuberculosis and 5) final medical evaluation done by a Specialist in Infectious Diseases which excluded active disease. All five criteria must be met. One TST is scheduled for each participant. Furthermore, the study does not provide follow-up. Each participant continues regular annual follow-up as per routine clinical practice.

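### The QuantiFERON level is listed as a risk factor in the regression of latent TB infection, although a positive QuantiFERON is one of the criteria that define the infection

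*Protocol article*

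**What the plan says.** **Outcome.** Under Primary outcome, LTBI rests on five criteria: a positive TST at enrollment, conversion from an earlier negative TST, a positive QFT, chest imaging without signs of active disease, and a specialist evaluation excluding active disease. The third is a "subsequent positive QuantiFERON-TB Gold (QFT) test result performed on the same day as the positive TST result" or within 5 days of conversion, with a response above 0.35 IU/ml in at least one of the two tubes. The section adds: "All five criteria must be met".

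**Predictors.** Secondary outcomes lists the QFT level (TB Ag-Nil) among the possible risk factors to be recorded. Data management plans repeats it with the qualifier that it is used where available. Statistical analysis states "Logistic regression analysis will be performed to assess the association between LTBI and possible risk factors", and its list of factors includes "median QuantiFERON-TB Gold In-Tube level (TB Ag-Nil) if available".

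**Prediction.** The same section says that "machine learning techniques will be used to predict the presence of LTBI with respect to health data and identified risk factors", and names as the final deliverable a decision support system that issues alerts for LTBI.

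**Source model.** The Introduction says the project is inspired by a TB risk model that "combines a quantitative measure of T cell sensitization and clinical covariates". It describes that model as predicting incident TB. The predictors it says were adopted are exposure, HIV status and transplant history.

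**The concern.** A covariate that is part of the outcome definition cannot be a risk factor for that outcome. Its association with LTBI is fixed in advance by the case definition (incorporation bias). At stake are the two secondary outcomes: the identification of risk factors and the validation of the prediction models. In a joint model, such a term can also distort the estimates for the factors of real interest, such as exposure, occupation and BCG history. If it reached the alert system, the alert would largely repeat a test result already in the file. Validation in a new cohort under the same case definition would not reveal this, because the overlap would be built into that cohort too.

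**Working it through.** **Inputs from the article.** Assumed prevalence 1%, precision 0.3%, confidence 90%, sample sizes 2,977 and 3,503 (The sample size); QFT cut-off 0.35 IU/ml and the five joint criteria (Primary outcome).

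**Assumptions, because the article gives no figure.** TST-positive share 2-10%; share of TST-positive, QFT-positive participants failing criterion 2, 4 or 5: 0-30%; QFT done only after a positive TST; log-normal QFT levels above the cut-off.

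**1. The plan's own figure.** n = Z² P(1−P)/d² = 1.645² × 0.01 × 0.99 / 0.003² = 2,976.6, so 2,977. The printed Z of 1.64 gives 2,959, a rounding difference. The point does not depend on this figure. Expected cases are 2,977 × 0.01 = 29.8 and 3,503 × 0.01 = 35.0, so about 30 to 35.

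**2. Definition against covariate.** All five criteria are required, so P(LTBI | both tubes at or below 0.35 IU/ml) = 0. No case can lie there, whatever the biology. This holds in one direction only: a value above the cut-off does not make a case, because the other four criteria must also be met.

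**3. Limiting case.** Suppose every TST-positive, QFT-positive participant is a case. Among those with a QFT value, all cases then lie above the cut-off and all non-cases at or below it. The AUC of the level is 1.0 and no finite maximum-likelihood estimate exists. In simulations at n = 3,503 with sex and QFT level as covariates, the fit failed or was degenerate in 200 of 200 runs at each TST-positive share tried (2%, 5%, 10%).

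**4. Away from the limit.** Suppose 10-30% of QFT-positives fail another criterion and so are non-cases above the cut-off. The AUC of the level among TST-positives is then 0.78-0.99 (TST-positive share 2-10%, n = 2,977). With 35 cases and 3-5% of 3,503 TST-positive, there was no separation and the fit converged in 300 of 300 runs in every scenario. The odds ratio is finite, but its size moves widely with the assumed levels and failure share, so none is quoted. In no run did a case lie below 0.35.

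**5. Availability.** If a QFT value exists only after a positive TST, having a value amounts to meeting criterion 1. Used alone as a yes/no predictor in the whole cohort, it has sensitivity 1, specificity 1 − (t − 0.01)/0.99 for TST-positive share t, and AUC = (1 + specificity)/2.
- t = 2%: specificity 0.990, AUC 0.995
- t = 5%: specificity 0.960, AUC 0.980
- t = 10%: specificity 0.909, AUC 0.955

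Coding the missing values as a category would therefore bring the TST result in by another route.

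**6. Complete cases.** If all terms were fitted jointly on participants with complete data, those retained out of 3,503 would be 3,503 × 0.03 = 105, × 0.05 = 175 or × 0.10 = 350. The loss is 97%, 95% or 90%, nearly all of it TST-negative participants.

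**7. The source model.** A T-cell measure can predict incident TB because later disease is not defined by that measure. Here the outcome is LTBI, which is. The article also does not list that measure among the predictors it adopted.

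**The case against.** The strongest reply is that the consequences depend on things the article does not fix. Much of it stands.

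- **Infinite odds ratios.** A reader might infer that the regression must break down. It need not. A continuous level separates the groups only if no non-case exceeds the lowest case, and participants above the cut-off who lack a documented earlier negative TST, or who fail imaging or the specialist evaluation, are non-cases. An AUC of 1.0 is the limiting case.
- **Loss of over 95% of the sample.** The article does not specify a complete-case analysis, and missing-data handling may sit in an analysis plan that is not shown. The TST-positive share is not given either. Data management plans also says that QFT conversions are collected, which suggests that some earlier QFT results exist. The loss is conditional.
- **Spoiled estimates for all other factors.** This needs a joint model. The article says only that logistic regression will be used; in single-factor fits the other estimates are untouched.
- **A circular alert system.** The article names no final predictors for the machine-learning step, so this cannot be read as a settled plan.
- **The word median.** It may be a descriptive item carried over from the list of recorded variables. That is a wording matter, and nothing here rests on it.

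None of this removes the overlap. The QFT level is named in the covariate list of a regression whose outcome requires a positive QFT. No section restricts the term to an earlier test or to descriptive use. The qualifier about availability gives no date that would separate it from the diagnostic test.

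**Conclusion.** The point holds as an incorporation problem: as written, the regression enters a defining component of LTBI as a risk factor for LTBI. This conclusion follows from the text alone and needs no assumption. The size of the damage does need assumptions. It runs from complete separation, if every TST-positive, QFT-positive participant is a case, to a finite but uninterpretable odds ratio with an AUC of 0.78-0.99 among TST-positives if 10-30% are not. The 90-97% loss applies only to a joint complete-case fit with 3-10% TST-positive and QFT values confined to them. For the alert system there is a risk of circularity if QFT is carried forward as an identified risk factor, and no more than that. The problem is confined to the secondary risk-factor and prediction analyses; the primary prevalence estimate is unaffected.

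**What to change.** In Secondary outcomes, Data management plans and Statistical analysis, take the diagnostic QFT level out of the list of possible risk factors for LTBI. State that neither it, nor the TST result, nor the availability of a QFT value may enter the logistic regression or the prediction models. Keep recording the level and report it descriptively among those tested.

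Alternatively, if an earlier QFT is what is meant, say so: only a result dated before the diagnostic work-up may enter, with a note of how many participants have one.

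Either option is a text change in three places and needs no new data. The retrospective analysis was due by November 2024, so if a first predictive model has already been fitted with the QFT level, it should be refitted without it before validation in the new cohort.

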### Design

The Evolution of CROSSWORD study includes a retrospective phase focused on the analysis of data derived from the ongoing CROSSWORD Study conducted at Fondazione Policlinico Universitario A. Gemelli IRCCS (FPG) and Università Cattolica del Sacro Cuore (UCSC) in Rome, Italy. The subsequent prospective phase will collect data from two centers in southern Italy, the University of Palermo (UNIPA) and the University of Bari (UNIBA)/ University Hospital of Bari. It is part of the national research project “DARE - Digital Lifelong Prevention”, funded by the Ministry of University and Research (MUR) as part of the National Plan for Complementary Investments to the PNRR, with the goal of maximizing the potential of data to enhance health promotion and enable lifelong prevention. DARE focuses on improving health trajectories by leveraging data. Furthermore, DARE Project aims to create a community focused on digital prevention through research, innovation, and engagement of all stakeholders [28].

With the support of the University of Bologna, partner of the national DARE project, the Research Team will then proceed with the analysis of the data collected at three clinical centers and the definition of a single data platform necessary for the assessment of the prevalence of LTBI and the identification of risk factors. Furthermore, prediction algorithms will be validated in all university hospitals involved through the recruitment of a new cohort of HCWs and students.

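### Centre and study phase are not named in the pooled risk-factor analysis, and the single prevalence figure depends on the mix of health-care workers and students; the size of any centre effect is not known from the document.

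*Protocol article*

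**What the plan says.** The Design section says that the study "includes a retrospective phase focused on the analysis of data derived from the ongoing CROSSWORD Study conducted at Fondazione Policlinico Universitario A. Gemelli IRCCS" (with the associated university in Rome). It continues: "The subsequent prospective phase will collect data from two centers in southern Italy", namely Palermo and Bari. Next comes the "analysis of the data collected at three clinical centers and the definition of a single data platform", which serves both the prevalence estimate and the risk-factor analysis. The timeline section starts the retrospective phase in November 2021 and the multicentre prospective phase in September 2024.

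The Statistical analysis section plans chi-squared tests for categorical variables and a logistic regression of latent infection on possible risk factors. The named covariates run from age and sex to "occupation, working/ training Unit and years working as HCWs". Results are then to be stratified by sex, nationality, TB incidence in the country of birth, BCG vaccination and change of role. Centre and phase are in neither list, nor in the risk-factor list under Secondary outcomes.

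The primary outcome is one prevalence over health-care workers and students together. The sample size section cites a "rate of LTBI prevalence of 2.1% in a population of Italian HCWs in Rome" and a "prevalence rate of LTBI of 0.62% among Italian healthcare students and postgraduates in Palermo", then assumes 1% in each hospital.

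**The concern.** The introduction gives the single-centre nature of the parent study as its main weakness, and this extension adds centres to overcome it. Once three hospitals are pooled, centre is a potential confounder of every risk factor whose frequency varies between them; BCG history, occupation mix, years worked and time spent abroad are plausible examples. On the Design section's description, the Rome v south contrast is also a contrast of retrospective v prospective collection, roughly three years apart. If centre is not in the model, that combined difference can load onto individual risk factors, and a prediction model built on them may partly learn site instead of risk. The chi-squared comparisons adjust for nothing, so they are the most exposed.

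The same mixing affects the primary outcome. If workers and students differ in prevalence, the overall proportion depends on how many of each happen to attend and consent at each site.

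**Working it through.** **Inputs from the sample size section.** Prevalence 2.1% (workers, Rome) and 0.62% (students and postgraduates, Palermo); planning value P = 1%; margin d = 0.3%; 90% confidence; total of 2,977; design odds ratio (OR) 1.69, for which 3,503 are stated.

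**Inputs assumed here, because the document does not give them.** Share of workers in the sample, relative size of the sites, and frequency of a risk factor at each site.

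**1. The plan's own figure.** n = Z²P(1−P)/d² = 1.645² × 0.01 × 0.99 / 0.003² = 2,976.6, which rounds up to 2,977. The printed Z of 1.64 gives 2,959. The figure reproduces, as a total at a common 1%.

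**2. Gap between the two cited rates.** 2.1/0.62 = 3.39. As an odds ratio, (0.021/0.979)/(0.0062/0.9938) = 3.44. This compares workers in one city with students and postgraduates in another, so it does not isolate a centre effect.

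**3. Illustration for an unadjusted table.** Take two equal sites with risks 2.1% and 0.62%, and a factor with no effect held by a fraction a at the first site and 1−a at the second. Risk in holders: a × 0.021 + (1−a) × 0.0062. Risk in non-holders: (1−a) × 0.021 + a × 0.0062.

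| Factor frequency at the two sites | Risk, holders | Risk, non-holders | Crude OR |
|---|---|---|---|
| 60% v 40% | 1.508% | 1.212% | 1.25 |
| 70% v 30% | 1.656% | 1.064% | 1.57 |
| 80% v 20% | 1.804% | 0.916% | 1.99 |

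If Rome's share varies from one third to about two thirds, the first row runs from 1.27 down to 1.18 and the second from 1.62 down to 1.42. With equal frequencies at both sites the crude OR is 1.00.

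**4. A smaller assumed gap.** If the centre OR were only 2 (say 1.33% v 0.67%), the same calculation gives 1.31 at 70/30% and 1.50 at 80/20%.

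**5. Pooled prevalence by mix.** With worker share w, the pooled prevalence is w × 2.1% + (1−w) × 0.62%. The 90% half-width is 1.645 × √(P(1−P)/2,977).

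| Assumed worker share | Pooled prevalence | Half-width at 2,977 |
|---|---|---|
| 25% | 0.99% | 0.30% |
| 50% | 1.36% | 0.35% |
| 75% | 1.73% | 0.39% |

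The planning value of 1% corresponds to w = (1 − 0.62)/(2.1 − 0.62) = 0.257, about 26% workers.

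**6. Information available.** Expected cases at 1%: 2,977 × 0.01 ≈ 30; 3,503 × 0.01 ≈ 35.

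**The case against.** The strongest reply is that none of these odds ratios describes the planned model. The 3.4-fold gap mixes occupation with city. The occupation variable separates doctors, nurses and others from preclinical and clinical students, and age and years worked are covariates too. Much of the gap may therefore already be adjusted for, and the document gives no prevalence for one population at two centres. This stands. A reader might infer that 1.25 to 2.0 is the bias in the adjusted results, but the document does not support that.

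The covariate list is introduced as inclusive rather than exhaustive, and an article condenses a fuller protocol. This carries some weight. Still, the article sets out long lists of covariates and stratifiers and assumes the same prevalence in each hospital, so an analysis run as described would not contain centre.

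Three other strong readings also fail:

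- **Unit cannot stand in for hospital.** The coding of working or training unit is not given, so it may or may not identify the hospital.
- **Centre and phase are wholly confounded, so a centre term always absorbs phase.** The Design section points that way for the data used to build the models. However, Setting and Participants also list Rome as recruiting, Palermo and Bari share a phase, and for the later validation cohort "prediction algorithms will be validated in all university hospitals involved through the recruitment of a new cohort of HCWs and students".
- **The prevalence has no target population.** Participants names one: all workers and students of the three hospitals. The open question is how well the enrolled mix represents it.

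The precision loss is modest. At a 50:50 mix the half-width is 0.35% with 2,977 subjects and 1.645 × √(0.0136 × 0.9864/3,503) = 0.32% with 3,503.

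**Conclusion.** The point holds in a limited form. As described, the pooled three-centre analysis has no named term for centre or phase, and its chi-squared comparisons are unadjusted, so factors distributed unevenly across sites can absorb a site or period difference. How much of this would remain in the adjusted model cannot be determined from the document. The crude odds ratios of about 1.25 to 2.0 rest on two equal sites at 2.1% and 0.62% and on assumed factor frequencies. They show only that, in unadjusted tables, the distortion could be of the same order as the design odds ratio of 1.69.

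The overall prevalence depends on the worker and student mix, ranging from 0.99% to 1.73% over assumed worker shares of 25% to 75% if the two cited rates apply. This limits the interpretation of a single figure but does not invalidate it. The correction is worth making before the pooled analysis.

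**What to change.** - Add centre (three levels) as a fixed effect to the logistic models. If Rome contributes data to both phases, add a phase term as well.
- Stratify the tabular comparisons by centre, for example with Cochran-Mantel-Haenszel tests.
- Report prevalence by centre and by worker or student group, with confidence intervals, next to the overall figure. If staff and student counts for the three hospitals can be obtained, standardise the overall figure to them; the document does not give these counts.
- State in the report that place and period cannot be separated for the Rome v south contrast where Rome supplies only retrospective data.

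**Cost.** Hospital and occupation should already be on record, so no new data are needed for the models and tables. Centre adds two coefficients to a model that already has about ten factors, several with many levels, and only about 30 to 35 expected cases. Some precision will be lost; penalised estimation can handle the sparse data. Intervals by centre will be wide: with 2,977 split equally (about 992 each, assumed) and 1% prevalence, the 90% half-width is 1.645 × √(0.01 × 0.99/992) = 0.52%.
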